# 8.0 Protocol Monitoring

The trial will be conducted in compliance with this protocol, International Conference on Harmonization (ICH) Guideline for Good Clinical Practices (GCP) and any applicable regulatory requirements. Monitors under contract with the RCHSPB will visit the clinical research site to monitor all aspects of the study in accordance with the appropriate regulations. The objectives of a monitoring visit will be: 1) to verify the prompt reporting of all data points, including reporting SAEs and checking availability of signed informed consent, 2) to compare individual subject records, CRIMSON data pulls and the source documents (supporting data, laboratory specimen records and medical records to include physician progress notes, nurses’ notes, subjects’ hospital charts), 3) to ensure protection of study subjects, compliance with the protocol, and accuracy and completeness of records. The monitors will also inspect the clinical site regulatory files to ensure that regulatory requirements (FDA/OHRP/ICH-GCP) are being followed. During the monitoring visits, the principal investigator (and/or designee) and other study personnel will be available to discuss the study progress and monitoring visit.

The principal investigator (and/or designee) will make study documents (eg. consent forms, CRIMSON data pulls) and pertinent hospital or clinical records readily available for inspection by the local IRB, the FDA, the site monitors, and the NIAID staff for confirmation of the study data.

**8.1 Data Safety Monitoring Board**

The NIAID Data Safety Monitoring Board (DSMB) will be asked to monitor the progress of the study while still blinded to the investigators. The NIAID Intramural DSMB is constituted to review the safety data of all NIAID-sponsored clinical studies that require DSMB oversight and consists of experts in infectious diseases, biostatistics, and clinical trials. The DSMB will review cumulative study data twice per year to evaluate safety, study conduct, and scientific validity and integrity of the trial. As part of this responsibility, DSMB members must be satisfied that the timeliness, completeness, and accuracy of the data submitted to them for review are sufficient for evaluation of the safety and welfare of study participants. The DSMB will also assess the performance of the overall study operations and any other relevant issues as necessary.

In addition to the biannual meetings, the DSMB will meet to review the data when 8 patients (47% of total expected enrollment) have been enrolled and have completed the treatment period. The group will also convene on an urgent basis if two or more subjects meet criteria for stopping study drug (see **section 6.3**) due to toxicities.

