**6.3 Criteria for stopping study drug and immediate institution of drug elimination procedure**

If a patient meets any of the following criteria for stopping study drug, his dosing assignment will be unblinded and if he was receiving leflunomide, he will be started immediately on the drug elimination procedure:

1. Patient develops malignancy or serious infection
2. Patient becomes pregnant
3. Patient develops elevation of liver enzymes greater than 2X the upper limit of normal (if liver enzymes are 3 X the upper limit of normal the study drug will be stopped immediately; if liver enzymes are >2 but <3 X the upper limit of normal, they will be repeated in 24 to 72 hours and if they remain >2 X the upper limit of normal the study drug will be stopped)
4. Patient develops grade III or IV adverse event or toxicity
5. Patient develops grade II or greater allergic reaction or urticaria
6. Patient develops a drop in CD4+ T cell count of 40% of baseline or a CD4+ T cell count of <200 that is confirmed with a second measurement (after 10-14 days) [Baseline CD4+ T cell count = average of CD4+ T cell count at H&P and Day 1]
7. Patient develops a medical condition that in the opinion of the investigator indicates that discontinuing the study drug is in the subject’s best interest

Additional criteria for stopping study drug:

1. It is felt by the principal investigator to be in the patient’s best interest, even if the patient does not agree
2. The patient begins taking any of the contraindicated medications listed in Appendix A or B or any other medication listed as an exclusion criteria and does not agree to discontinue it
3. The patient begins taking antiretroviral medications
4. Patient desire to leave study
5. Patient noncompliance
6. Termination of study

At the time of withdrawal from study, a member of the study team (the study coordinator, principal investigator, associate investigator or covering physician) will contact the pharmacy for unblinding of treatment arm (PDS during business hours Monday through Friday or inpatient pharmacy after hours and on weekends). If a patient was receiving leflunomide, oral cholestyramine 8 g three times daily will be administered for a total of 11 days. Serum A77 1726 level will be measured upon completion of this procedure. If the A77 1726 level is above 0.02 mg/L, the elimination procedure will be repeated.

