6.4 Criteria for stopping enrollment

A Data Safety Monitoring Board (DSMB) will meet at a predetermined time (when 8 subjects have completed the 28 day active treatment phase) as well as on an urgent basis if 2 or more patients meet criteria for stopping study drug due to adverse events that are possibly, probably, or definitely related to the study drugs. This board will review safety data and determine whether the study should continue enrollment and/or study drug dosing. If enrollment is closed and the study terminated, the dosing arm of those patients who are enrolled at that time and receiving the study drug will be unblinded. As soon as possible, a member from the pharmacy will inform the study coordinator of the patient’s treatment arm, and the study coordinator will inform the patient. Those patients who had been receiving leflunomide will undergo the drug elimination procedure.

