7.2.1 Reporting to the IRB

The following types of serious adverse events, regardless of relationship to study drug, will be reported to the IRB by fax or phone within 24 hours of awareness of the event followed by written SAE form within 3 days of awareness of event:

- Death
- Life-threatening event
- Cancer occurring on study
- Pregnancy
- Congenital anomaly/birth defect
- Permanent disability/incapacity

The following types of serious adverse events will be reported to the IRB by written SAE form within 3 days of knowledge of the event:

- Grade 3 and 4 adverse events
- Hospitalizations
- Adverse events of any toxicity considered serious by the principle investigator
- Any other event or condition which in the judgment of the principle investigator represents a significant hazard

The following types of adverse events will be reported to the IRB at annual review of the protocol:

- Grade 2 adverse events except those determined to be unrelated or unlikely to be related to study drug (Grade 3 and 4 adverse events will be reported as described above)

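### The urgent DSMB trigger needs two patients stopped for toxicity whatever the grade; one related death or life-threatening event obliges neither a prompt DSMB review nor a pause in randomisation

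*Protocol*

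**What the plan says.** Section 8.1 states the urgent trigger for stops caused by toxicities: "The group will also convene on an urgent basis if two or more subjects meet criteria for stopping study drug". It keeps a review at 8 completers and adds a routine cycle: "The DSMB will review cumulative study data twice per year". It also gives the board a general remit: "The DSMB will also assess the performance of the overall study operations and any other relevant issues as necessary".

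Section 6.4 has the same 8-completer review and the same count: "as well as on an urgent basis if 2 or more patients meet criteria for stopping study drug due to adverse events". It narrows which events qualify, namely those "that are possibly, probably, or definitely related to the study drugs". It then gives the board the decision: "This board will review safety data and determine whether the study should continue enrollment and/or study drug dosing".

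The stopping criteria are in section 6.3. They include any grade III or IV event and, at the mild end, liver enzymes above 2 but below 3 times ULN: "they will be repeated in 24 to 72 hours and if they remain >2 X the upper limit of normal", study drug is stopped.

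Deaths and life-threatening events have their own reporting route. Under section 7.2.1 they go quickly to the IRB whatever their relationship to study drug: "will be reported to the IRB by fax or phone within 24 hours of awareness of the event". Under section 7.2.2 they go to the sponsor's safety department within 1 business day and, if possibly related, to the FDA within 7 calendar days. Neither section names the DSMB as a recipient.

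**The concern.** The rule counts patients and ignores severity. Two mild, confirmed enzyme rises judged possibly related compel an urgent meeting, while one related death counts as a single stop and compels none. The body that section 6.4 charges with the enrolment decision is therefore obliged to respond to the weaker signal and not to the graver one.

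This matters more in a small trial. With 12 leflunomide patients, a first related fatal or life-threatening event may be the only warning. Section 9.2 states that participants gain no immediate clinical benefit, and section 9.3.1.1 lists rare fatal liver injury, sepsis and interstitial lung disease. As written, further patients could be randomised before the board has reviewed such an event.

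**Working it through.** **Reading the sections together**

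| Event | Counts towards the two? | Urgent DSMB meeting required? | Randomisation paused by the protocol? |
|---|---|---|---|
| Two patients, enzymes 2 to 2.5 times ULN, confirmed and possibly related (Grade 1 for AST/ALT, Appendix D) | Yes, both | Yes (6.4, 8.1) | No; the board decides when it meets |
| One related death or life-threatening event, no other related stop | Yes, as one | No | No |
| Two stops for non-compliance or patient choice (6.3) | No | No | No |

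Section 6.3 stops and unblinds the affected patient, and starts washout if that patient was on leflunomide. It does nothing about new patients. Section 7.2 creates reporting duties only. The next review the protocol requires is then the twice-yearly meeting (up to 12/2 = 6 months away if meetings are evenly spaced) or the 8-completer review, whichever falls first.

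**How often it could arise**

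The protocol has no figure to reproduce here and gives no event rate. The only input it supplies is n = 12 leflunomide patients (section 4.3). The rest are assumptions: p, the per-patient risk of a related fatal or life-threatening event, 0.1% or 1%; q, the risk of stopping for a lesser related toxicity, 5% or 10%. Patients are taken one after another, and placebo events judged related are ignored. All results are chances per trial.

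- A. Any such event: 1 − (1 − p)^12.
- B. The first such event arrives with no earlier related stop, so no meeting is required then: p/(p + q) × [1 − (1 − p − q)^12].
- C. Such an event occurs and the two-patient trigger is never met: 12 × p × (1 − p − q)^11.

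For p = 1%, q = 5%:
- A = 1 − 0.99^12 = 0.1136.
- B = (0.01/0.06) × (1 − 0.94^12) = 0.1667 × 0.5241 = 0.0873.
- C = 0.12 × 0.94^11 = 0.12 × 0.5063 = 0.0608.

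| p | q | A | B | C |
|---|---|---|---|---|
| 1% | 5% | 11.4% | 8.7% | 6.1% |
| 1% | 10% | 11.4% | 6.8% | 3.3% |
| 0.1% | 5% | 1.2% | 0.91% | 0.67% |
| 0.1% | 10% | 1.2% | 0.71% | 0.37% |

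For contrast, two or more lesser stops alone, 1 − (1 − q)^12 − 12q(1 − q)^11, would require an urgent meeting in 11.8% (q = 5%) or 34.1% (q = 10%) of trials.

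**What these figures do not measure**

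B and C are chances that the rule requires no meeting. They are not chances of harm. A pause could avert only a second severe event. The chance of two or more, 1 − (1 − p)^12 − 12p(1 − p)^11, is about 0.6% at p = 1% and about 0.007% at p = 0.1%, and only part of that is preventable.

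**The case against.** The strongest reply is that this is a design choice with other safeguards around it. The two-patient rule sets a minimum, and section 8.1 lets the board take up other relevant issues. NIAID is the IND sponsor and the board is NIAID's own, so its parent institute hears of a death within 1 business day. The IRB and FDA are told as well, and any of them could halt the trial. The board is a standing one shared across studies, so its operating procedures may lie outside this protocol.

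The event is also unlikely. The label calls severe liver injury rare and places most cases among patients with multiple risk factors. Section 5.2 excludes hepatitis B and C, alcohol abuse, abnormal liver tests, interstitial lung disease and patients who will not stop hepatotoxic drugs. Exposure is 28 days at 20 mg, followed by washout.

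Most of this stands, and it limits the point. A reader might infer that the board may not meet after a single death, or that nobody would act for six months. The documents do not support that: they show only that this protocol does not require the board to look. Nor do they support reading the low enzyme threshold as a fault, since it is deliberate caution, or reading the trigger as any two drug-stops, since only toxicity-related stops count.

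What remains is that the sponsor made one trigger mandatory and left the graver event to discretion. Reporting to other bodies narrows that gap without closing it.

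**Conclusion.** The point holds as a gap in a stated rule. Sections 6.4 and 8.1 fix a numeric trigger without regard to severity. No section requires the DSMB to review a single related death or life-threatening event before its next scheduled meeting, or pauses randomisation until then. This conclusion rests on the text and does not depend on the assumed rates.

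The practical size is small. Such an event would occur in about 1% to 11% of trials across the assumed risks, and a second one in well under 1%. A reader might take the figure of about 9% as the chance that patients are harmed by the missing trigger. It is not: it includes events in the last patients treated and events shortly before a scheduled review. Endpoint, analysis and power are untouched. The change should be made as a low-probability safety safeguard. Confidence is medium, because standing board procedures cannot be seen.

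**What to change.** Add to sections 6.4 and 8.1:

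*The DSMB will also convene urgently for any single death or life-threatening adverse event judged at least possibly related to study drug. New randomisation will be paused until the DSMB has reviewed the event. At that review the DSMB will also decide whether patients already on study drug continue dosing.*

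Leave the two-patient trigger unchanged and without an automatic pause, so that two Grade 1 enzyme rises do not freeze the trial. The decision on enrolment stays with the board, as section 6.4 already provides.

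The cost is three sentences and, only if such an event occurs, one unscheduled meeting and a short enrolment delay. Section 4.4.1 limits screening to 28 days, so some screened patients may have to be re-screened if their window lapses during the pause. The accrual ceiling of 40 in section 4.3 leaves 40 − 18 = 22 places for patients who screen but do not enrol.

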# 9.0 Human Subjects Protection

**9.1 Subject selection criteria**

Patients will be recruited for participation in this study without bias to gender, racial, economic, or social status. Patients new to the NIH will be recruited from outside physician referrals. Subjects will be recruited from NIH clinics and local public, academic, and private clinics. The study will be advertised and posted on the NIH web site.

The safety of leflunomide in the pediatric population has not been studied, and its use is not recommended in children. Therefore children (age <18 years) will be excluded from this study.

**9.2 Benefits**

There are no immediate clinical benefits for patients who participate in this study. However, the study will make a significant contribution to the knowledge of HIV immunopathogenesis with potential therapeutic implications for the future.

**9.3 Risks**

The potential risks of this study are:

- It is possible that treatment with leflunomide will lead to more adverse events or fluctuation in HIV viral load
- Risks of the medications: leflunomide and cholestyramine, which are discussed below

**9.3.1 Specific medication risk**

**9.3.1.1 Leflunomide**

As outlined in the package insert (submitted separately), the safety of leflunomide was examined in three clinical trials that enrolled a total of 1839 patients with active rheumatoid arthritis of whom 816 received leflunomide and 1023 received either placebo, methotrexate, or sulfasalazine. Patients in these clinical trials received an initial loading dose of leflunomide of 100 mg per day for 3 days followed by maintenance therapy with 20 mg/day.

Leflunomide is contraindicated in two patient populations: 1) patients with known hypersensitivity to leflunomide, and 2) women who are or may become pregnant. The package insert contains a box warning that states pregnancy must be excluded before the start of treatment with leflunomide, and pregnancy must be avoided during leflunomide treatment or prior to the completion of the drug elimination procedure after leflunomide treatment.

Leflunomide can cause fetal harm when administered to a pregnant woman. When administered orally to rats during organogenesis at a dose of 15 mg/kg, leflunomide was teratogenic (most notably anophthalmia or microophthalmia and internal hydrocephalus). The systemic exposure of rats at this dose was approximately 1/10 the human exposure level based on AUC. Under these exposure conditions, leflunomide also caused a decrease in the maternal body weight and an increase in embryo lethality with a decrease in fetal body weight for surviving fetuses. In rabbits, oral treatment with 10 mg/kg of leflunomide during organogenesis resulted in fused, dysplastic sternebrae. The exposure level at this dose was essentially equivalent to the maximum human exposure level based on AUC. At a 1 mg/kg dose, leflunomide was not teratogenic in rats or rabbits.

When female rats were treated with 1.25 mg/kg of leflunomide beginning 14 days before mating and continuing until the end of lactation, the offspring exhibited marked (greater than 90%) decreases in postnatal survival. The systemic exposure at 1.25 mg/kg was approximately 1/100 the human exposure level based on AUC.

The package insert for leflunomide also contains several warnings:

- Immunosuppression Potential/Bone Marrow Suppression: leflunomide is not recommended in persons with severe immunodeficiency, bone marrow dysplasia, or severe uncontrolled infections. Rarely, severe infections including sepsis, which may be fatal, have been reported in patients receiving leflunomide. Most of the reports were confounded by concomitant immunosuppressant therapy and/or comorbid illness which, in addition to rheumatoid disease, may predispose patients to infection.

There have been rare reports of pancytopenia, agranulocytosis, and thrombocytopenia in patients receiving leflunomide alone. These events have been reported most frequently in patients who received concomitant treatment with methotrexate or other immunosuppressive agents, or who had recently discontinued these therapies; in some cases, patients had a prior history of a significant hematologic abnormality.

- Hepatotoxicity: Rare cases of severe liver injury, including with fatal outcome, have been reported during treatment with leflunomide. Most cases of severe liver injury occur within 6 months of therapy and in a setting of multiple risk factors for hepatotoxicity (liver disease, other hepatotoxins).

In clinical trials, leflunomide treatment as monotherapy or in combination with methotrexate was associated with elevations of liver enzymes, primarily ALT and AST, in a significant number of patients; these effects were generally reversible. Most transaminase elevations were mild (≤2-fold the upper limit of normal) and usually resolved while continuing treatment. Marked elevations (>3-fold the upper limit of normal) occurred infrequently and reversed with dose reduction or discontinuation of treatment.

- Pre-existing hepatic disease: Given the possible risk of increased hepatotoxicity, and the role of the liver in drug activation, elimation and recycling, the use of leflunomide is not recommended in patients with significant hepatic impairment or evidence of infection with hepatitis B or C viruses.
- Skin reactions: Rare cases of Stevens-Johnson syndrome and toxic epidermal necrolysis have been reported in patients receiving leflunomide.
- Malignancy: The risk of malignancy, particularly lymphoproliferative disorders, is increased with the use of some immunosuppression medications. There is a potential for immunosuppression with leflunomide. No apparent increase in the incidence of malignancies and lymphoproliferative disorders was reported in the clinical trials of leflunomide, but larger and longer-term studies would be needed to determine whether there is an increased risk of malignancy or lymphoproliferative disorders with leflunomide.

The package insert also contains the following precaution:

- Respiratory: Interstitial lung disease has been reported during treatment with lefunomide and has been associated with fatal outcomes. Interstitial lung disease is a potentially fatal disorder, which may occur acutely at any time during therapy and has a variable clinical presentation. New onset or worsening of pulmonary symptoms, such as cough and dyspnea, with or without associated fever, may be a reason for discontinuation of therapy and for further investigation as appropriate.

Adverse reactions associated with the use of leflunomide in rheumatoid arthritis include diarrhea, elevated liver enzymes, alopecia and rash. In the controlled studies, the following adverse events were reported, regardless of causality: allergic reaction (1-5%), asthenia (3-6%), flu syndrome (0-4%), infection (0-4%), injury accident (5-7%), pain (1-4%), abdominal pain (5-6%), back pain (5-8%), hypertension (9-10%), chest pain (1-2%), anorexia (3%), diarrhea (17-27%), dyspepsia (5-10%), gastroenteritis (1-3%), abnormal liver enzymes (5-10%), nausea (9-13%), mouth ulcer (3-5%), vomiting (3-5%), hypokalemia (1-3%), weight loss (2-4%), arthralgia (1-4%), leg cramps (0-4%), joint disorder (2-8%), synovitis (1-4%), tenosynovitis (2-5%), dizziness (4-7%), headache (7-13%), paresthesia (2-4%), bronchitis (5-8%), increased cough (3-5%), respiratory infection (15-27%), pharyngitis (2-3%), pneumonia (2-3%), rhinitis (2-5%), sinusitis (1-5%), alopecia (9-17%), eczema (1-3%), pruritus (4-6%), rash (10-12%), dry skin (2-3%), urinary tract infection (5%).

In addition the following side effects have been reported in 1% to <3% of the rheumatoid arthritis patients in the leflunomide treatment group in controlled trials.

- Body as a whole: abscess, cyst, fever, hernia, malaise, pain, neck pain, pelvic pain
- Cardiovascular: angina pectoris, migraine, palpitation, tachycardia, varicose vein, vasculitis, vasodilation
- Gastrointestinal: cholelithiasis, colitis, constipation, esophagitis, flatulence, gastritis, gingivitis, melena, oral moniliasis, pharyngitis, salivary gland enlarged, stomatitis (or aphthous stomatitis), tooth disorder
- Endocrine: diabetes mellitus, hyperthyroidism
- Hemic and lymphatic system: anemia (including iron deficiency anemia), ecchymosis
- Metabolic and nutritional: creatinine phosphokinase increased, hyperglycemia, hyperlipidemia, peripheral edema
- Musculo-skeletal system: arthrosis, bone necrosis, bone pain, bursitis, muscle cramps, myalgia, tendon rupture
- Nervous system: anxiety, depression, dry mouth, insomnia, neuralgia, neuritis, sleep disorder, increased sweating, vertigo
- Respiratory system: asthma, dyspnea, epistaxis, lung disorder
- Skin and appendages: acne, contact dermatitis, fungal dermatitis, hair discoloration, hematoma, herpes simplex, herpes zoster, maculopapular rash, nail disorder, skin discoloration, skin disorder, skin nodule, subcutaneous nodule, skin ulcer
- Special senses: blurred vision, cataract, conjunctivitis, eye disorder, taste perversion
- Urogenital system: albuminuria, cystitis, dysuria, hematuria, menstrual disorder, prostate disorder, urinary frequency, vaginal moniliasis

Other less common adverse events seen in clinical trials include: 1 case of anaphylactic reaction occurred following restarting of drug after withdrawal due to rash; urticaria, increased eosinophil count, transient low platelet count, and low white bood cell count.

Since the licensing of leflunomide for public use, the following side effects have been reported rarely.

- Body as a whole: opportunistic infections, severe infections including sepsis that may be fatal;
- Gastrointestinal: pancreatitis
- Hematologic: low white blood cell count, low neutrophil count, low platelet count
- Hypersensitivity: angioedema
- Hepatic: hepatitis, jaundice, severe liver injury such as hepatic failure and acute hepatitic necrosis that may be fatal
- Respiratory: interstitial lung disease, including interstitial pneumonitis and pulmonary fibrosis, which may be fatal
- Nervous system: peripheral neuropathy
- Skin and appendages: erythema multiforme, Stevens-Johnson syndrome, toxic epidermal necrolysis

No evidence of carcinogenicity was observed in a 2-year bioassay in rats at oral doses of leflunomide up to the maximally tolerated dose of 6 mg/kg (approximately 1/40 the maximum human M1 systemic exposure based on AUC). However, male mice in a 2-year bioassay exhibited an increased incidence in lymphoma at an oral dose of 15 mg/kg, the highest dose studied (1.7 times the human M1 exposure based on AUC). Female mice in the same study exhibited a dose-related increased incidence of bronchoalveolar adenomas and carcinomas combined beginning at 1.5 mg/kg (approximately 1/10 the human M1 exposure based on AUC). The significance of the findings in mice relative to the clinical use of leflunomide is not known.

Leflunomide was not mutagenic in the Ames Assay, the Unscheduled DNA Synthesis Assay, or in the HGPRT Gene Mutation Assay. In addition, leflunomide was not clastogenic in the *in vivo* Mouse Micronucleus Assay nor in the *in vivo* Cytogenetic Test in Chinese Hamster Bone Marrow Cells. However, 4-trifluoromethylaniline (TFMA), a minor metabolite of leflunomide, was mutagenic in the Ames Assay and in the HGPRT Gene Mutation Assay, and was clastogenic in the *in vitro* Assay for Chromosome Aberrations in the Chinese Hamster Cells. TFMA was not clastogenic in the *in vivo* Mouse Micronucleus Assay nor in the *in vivo* Cytogenetic Test in Chinese Hamster Bone Marrow Cells.

